## Abstract

**Background:**

It is a recurring theme in clinical practice that patients using inhaled medications via an inhaler do not use their device to a standard that allows for optimum therapeutic effect, and some studies have shown that up to 90% of people do not use their inhalers properly. Observation and correction of the inhaler technique by health care professionals is advised by both national and international guidelines and should be performed at every opportunity to ensure that the optimum inhaler technique is achieved by the user. This study will provide a greater understanding of the most frequent technique errors made by people using 13 different inhaler types.

**Objective:**

This study aims to identify and compare inhaler technique errors and their prevalence in adults, using device-specific checklists in accordance with manufacturers’ guidelines, for 13 specific inhaler types across all lung conditions and to correlate these errors with possible determinants of poor technique. It also aims to assess the error frequency at each step in the device-specific questionnaires and compare the error rates among device types.

**Methods:**

In a single visit, participants using an inhaler included in the inclusion criteria will have their inhaler technique observed using an identical placebo device, which will be recorded using device-specific checklists, and technique-optimized, or switched to a suitable inhaler.

**Results:**

The study is already underway, and it is anticipated that the results will be available by 2022.

**Conclusions:**

The SCORES (Study to Investigate the Prevalence of Device-Specific Errors in Inhaler Technique in Adults With Airway Disease) study will ascertain the prevalence of device-specific inhaler technique errors at each step in the device-specific checklists, compare error rates among 13 device types, and correlate these errors with possible determinants of poor technique. Future work will involve the clarification and classification of these errors into *critical* and *noncritical* categories.

**Trial Registration:**

ClinicalTrials.gov NCT04262271; https://clinicaltrials.gov/ct2/show/NCT04262271

**International Registered Report Identifier (IRRID):**

DERR1-10.2196/26350

## Introduction

### Background

Inhaled medications are the cornerstone of pharmacological treatment for many lung conditions, such as asthma and chronic obstructive pulmonary disease (COPD), and the amount spent by the National Health Service (NHS) on inhaled medication is considerable [1], with poor inhaler technique accounting for additional indirect costs [2].

It is a recurring theme in clinical practice that patients with asthma and COPD alike do not use their inhalers to a standard that allows optimum therapeutic effect [3-7]. Many patients continue to make critical errors when using their inhalers; therefore, they do not realize or enjoy the benefits of optimal inhaled treatment. Consequently, the NHS spends millions of pounds on high-cost yet subtherapeutic treatment [8]. In addition, there is now a burgeoning number of inhaler devices available for patient use, which causes additional confusion among health care professionals on how to reliably evaluate and quantify a good inhaler technique to a standard that allows quality assurance [9,10].

Both the Global Initiative for Asthma (GINA) [11] and Global Initiative for Chronic Obstructive Lung Disease (GOLD) [12] place great importance on correcting poor inhaler technique before escalating inhaled therapy. There is also a large body of evidence reporting that inhalation errors are associated with worse disease outcomes in patients with asthma and COPD and that the time invested by health care professionals to correct patients’ inhaler technique is vital to improve health outcomes [13].

Other than device-specific checklists based on manufacturer’s guidelines, which are often not used or shared in any standardized fashion, there is currently no formal way of assessing and quantifying the inhaler technique errors (ITE) made by patients in a way that can be translated between health care environments. Divergence and heterogeneity between checklists for the same device in previously published studies makes direct comparison of results difficult; thus, development of common checklists has been recommended [14].

### Objectives

#### Overview

This study aims to identify ITE and their prevalence using device-specific checklists based on manufacturers’ guidelines for 13 inhaler types across all lung conditions and to correlate these errors with possible determinants of poor technique. It also aims to assess the error frequency at each step in the device-specific questionnaires, compare error rates among device types, and determine which of these errors are deemed *critical* or *noncritical*.

#### Primary Objective

The primary objective of this study is to assess the prevalence of device-specific ITE in 13 different devices, using the manufacturers’ guidelines.

#### Secondary Objectives

The secondary objectives are as follows:

To assess whether the frequency of ITE are associated with participant demographics, respiratory diagnosis, and comorbidities; disease control as measured by questionnaires, such as Asthma Control Questionnaire (ACQ) for asthma and COPD Assessment Tool (CAT) score for COPD, and participant clinical characteristics including exacerbation frequency within the past 12 months; length of time a participant has been using the observed inhaler, along with previous device-specific inhaler technique training (if and when previous training has taken place and given by whom); and levels of behavioral and adherence risk profile as measured by the social, psychographic, usage, and rational (SPUR) profiling tool (Observia).To assess the user error frequency at each step in the device-specific guidelines.To compare user error rates among device types.

#### Exploratory Objectives

The exploratory objectives are as follows:

To categorize ITE as *critical* or *noncritical* and prioritize the importance of these errors by conducting a further study outside the remit of this protocol and involves a Delphi consensus process. Owing to ongoing debate and variations in the definitions of critical and noncritical errors, final definitions will be based on the outcomes of the Delphi consensus process. The information from the Delphi process, along with the data from this prevalence study, will be collated to determine which ITE will be included in a subsequent study, in which a scoring system to quantify ITE will be developed.To correlate severity of disease with ITE if a disease-specific tool is available. The GINA step will be used for asthma and GOLD stage for COPD with spirometry, whereas forced expiratory volume in 1 second (FEV_1_), forced vital capacity (FVC), and FEV_1_/FVC ratio measurements will be used if spirometry is performed as part of standard care.

## Methods

### Overview

This is a prevalence study and includes both descriptive and analytical methods, analyzing the prevalence of ITE in adults with airway disease across 13 different inhaled devices.

### Eligibility Criteria

Participants will be drawn from a range of clinical conditions affecting adults that use an inhaler device. The inclusion and exclusion criteria are presented in Textbox 1.

Inclusion and exclusion criteria.
**Inclusion criteria**
Participants must be aged ≥18 years.Participants should have been prescribed (by a doctor or health care professional) 1 of 13 inhaler device types for an airways condition (Accuhaler, Autohaler, Breezhaler, Easi-breathe, Easyhaler, Ellipta, Genuair, Handihaler, Nexthaler, pressurized metered-dose inhalers, pressurized metered-dose inhalers plus spacer [eg, Aerochamber or Volumatic], Respimat, and Turbohaler).Participants should be able to provide written informed consent.
**Exclusion criteria**
Participants are currently on treatment with systemic steroids or antibiotics for an exacerbation of the participants’ airway condition.In the opinion of the investigator, the participant will be unable to perform the study procedures.

### Sampling and Sample Size

A minimum of 650 participants will be recruited for the study. To ensure an adequate sample size for each of the 13 different device types, a minimum of 50 participants will be recruited for each device group. Owing to the wide variety of devices involved in the study, it was not possible to conduct a power calculation because the device error frequency is known to be disparate among the inhalers involved. On the basis of existing recruitment numbers in published ITE trials [15], alongside the expert clinical opinion from within the protocol development team, a minimum of 50 participants using each device type was felt appropriate to provide a reasonable chance to identify a range of errors.

Potentially, participants may be using several different inhaler device types, so there could be a choice of device type to observe. Throughout the study, the study team will closely monitor the number of participants recruited using each of the 13 device types; therefore, to ensure that the risk of selection bias is distributed equally across all device types, the least commonly recruited device type will be observed in each participant.

Careful consideration has been afforded to ensure that adequate numbers of participants are recruited in all 13 device types included in the study. We will have access to more than 70,000 patients across the Wessex region using participant identification center ITE. Examination of primary care databases will identify those using the inhaler types included in this study, and invitations to participate will be sent to ensure recruitment across all device types.

Recruitment will last for up to 24 months and will not cease at the recruitment of 50 participants in each group, allowing sample sizes greater than this figure.

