#### Previous Inhaler Technique Training

The date of the participants’ most recent inhaler technique assessment for the device being observed during the study visit will be recorded in the CRF, along with the cadre of the person by whom it was assessed (eg, nurse, pharmacist, physiotherapist, or doctor). We will also record which inhaler device the participant is observed using and how long they have been using this device for.

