If a participant is observed making repeated errors using their device, despite inhaler technique correction, a more suitable inhaler device will be considered. If it is possible to obtain a prescription from a qualified health care professional for an alternative, more suitable device, then this device will be issued during the study visit. The participant will be taught how to use the new device and will be asked to demonstrate the correct technique as per standard clinical practice. Observations with ITE will be recorded in the participants’ CRF for the initial device only. A letter will be sent to the participants’ GP, informing them that a new inhaler device has been issued, with a request to add this to their future repeat prescriptions. If it is not possible to issue an alternative device, a letter will be sent to the participants’ GP recommending a change to a more suitable device, and the participant will require training in the use of this new device. If a participant is participating in another research trial, they will be encouraged to communicate any change in device type or medication with the investigators of the other trial.

If a participant has been prescribed and uses more than 1 inhaler device type, observation and correction of only one device type will be carried out.

To ensure that each member of the study team involved in the inhaler technique observation has the necessary expertise and to ensure standardization across device technique assessment, all members of the study team will attend regular training sessions that will continue every 3 months throughout the study to ensure that competencies have been maintained. Study investigators will have to demonstrate the perfect inhaler technique for each device to be deemed competent. A standard operating procedure for the correct inhaler technique for each device will be produced, and records of competencies will be kept in the study site file.

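### Observing each participant's least-recruited device evens out group counts, not selection bias: when recruitment is unequal, the commonest device groups lose their multi-device users

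*Protocol article*

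**What the plan says.** Sampling and Sample Size recognises that "participants may be using several different inhaler device types, so there could be a choice of device type to observe". The team is to watch the running count for each of the 13 types, and the stated aim and rule are: "the risk of selection bias is distributed equally across all device types, the least commonly recruited device type will be observed in each participant". The targets are stated as "A minimum of 650 participants will be recruited for the study" and "a minimum of 50 participants will be recruited for each device group". The same section says recruitment may continue past 50 in a group, and that invitations drawn from primary care databases will be used to reach every device type.

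Inhaler Technique Observation and Intervention adds that for a person with more than one type, "observation and correction of only one device type will be carried out".

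The Data Analysis overview expects that group sizes may differ and analyses a random 50 per device. The Primary Analysis compares error counts between device types by one-way ANOVA or Kruskal–Wallis, with no term for multi-device use. Of device-related items, Previous Inhaler Technique Training lists this: "We will also record which inhaler device the participant is observed using and how long they have been using this device for".

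**The concern.** The protocol credits the rule with a property it does not have. Each participant contributes one device, so for anyone with a choice the rule decides which group they join, and it favours whichever of their devices is behind in the count. Whether a person uses one or several types then affects group membership differently for commonly and rarely recruited devices. Drawing 50 at random from each group does not undo this, because the groups have already been sorted.

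The primary objective (error prevalence per device) and the primary analysis (devices compared on error counts) are both exposed. If multi-device users differ in technique, the estimates for the commonest devices lean towards people who use only that device, and part of any between-device difference reflects who was placed where.

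**Working it through.** **The plan's own figure.** 13 × 50 = 650, which reproduces the stated minimum. The issue is the make-up of the groups, so no sample-size formula applies.

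**Inputs.** From the article: 13 types, one device observed per person, least-recruited rule, random 50 per group analysed. Not in the article, and therefore assumed: the share of multi-device users, how often each device is used, and any extra errors made by multi-device users.

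**Check 1: by hand.** Per 100 participants, let 60 use a pressurized metered-dose inhaler (pMDI) plus one other device, 15 a pMDI alone and 25 another device alone, with the 12 other devices equally common.
- Even filling would give 100/13 = 7.7 per group. Sole pMDI users already number 15, so the pMDI group stays ahead and nearly all 60 go elsewhere.
- Multi-device share in the other groups: 60/(60 + 25) = 71%, which is also the true share among users of those devices.
- True share among pMDI users: 60/(60 + 15) = 80%. Observed in the pMDI group: near 0%.
- A random choice between a person's two devices would give 30/(30 + 15) = 67% for the pMDI and 30/(30 + 25) = 55% elsewhere.

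Now let the number w of sole pMDI users fall, other weights fixed. The even-fill group size is (85 + w)/13, and multi-device users enter the pMDI group only to the extent that w is below it.

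| w | Even-fill size | pMDI group, by hand | pMDI group, simulated (900 participants) | Other groups, simulated |
|---|---|---|---|---|
| 15 | 7.7 | 0% | 1–3% | about 70% |
| 8 | 7.2 | 0% | 9–12% | about 70% |
| 4 | 6.8 | (6.85 − 4)/6.85 = 42% | 47–49% | about 70% |
| 2 | 6.7 | (6.69 − 2)/6.69 = 70% | 72% | 68–69% |

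The simulated values sit somewhat above the hand values because running counts fluctuate.

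**Check 2: general device patterns.** Simulation of 13 devices and 1,000 participants, with multi-device users holding two types. Entries are the multi-device share in the commonest versus the rarest group under the protocol's rule.

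| Multi-device users overall | Skewed use (30% to 1%) | Moderate use (16% to 4%) | True share among each device's users |
|---|---|---|---|
| 20% | 0% vs 36% | 1% vs 32% | about 31–37% |
| 40% | 1% vs 56% | 6% vs 55% | about 54–62% |
| 60% | 10% vs 78% | 28% vs 75% | about 72–78% |

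The rarest groups match their own users; the commonest are depleted, and groups of middling frequency partly so. With equally used devices there is no gradient (38–43% in all groups when 40% are multi-device users). Random choice in the moderate pattern at 40% gives 38–42% in all groups.

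**Check 3: effect on the primary comparison.** 40% multi-device users, no true device difference, Poisson errors with mean 2, 50 sampled per group where available, Kruskal–Wallis at an assumed 0.05, 200 repetitions.

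| Extra errors in multi-device users | Rarest minus commonest (skewed; moderate) | Rejections, protocol's rule | Rejections, random choice |
|---|---|---|---|
| 0 | 0.0; 0.0 | 6%; 5.5% | 2.5%; 6.5% |
| 0.5 | 0.3; 0.3 | 7%; 10% | 4.5%; 3% |
| 1 | 0.6; 0.5 | 25.5%; 27% | 4%; 3.5% |

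Hand check, moderate pattern, one extra error: (0.55 − 0.06) × 1 = 0.49. With 200 repetitions the standard error of a 5% rate is √(0.05 × 0.95/200) = 1.5 percentage points, so 7% cannot be told from 5%.

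**The case against.** Much can be said for the rule. It is fixed in advance, so neither assessor nor participant picks the device to demonstrate, and that discretion is itself a source of selection bias. It also serves the 50-per-device minimum. Both merits stand, and they are reasons to keep it.

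The size is not known. The near-0% against 70% contrast comes from one assumed pattern. It shrinks as sole use of the commonest device falls and vanishes if recruitment is equal; targeted invitations may push that way. In addition, the 900-participant version with unequal other devices leaves some groups below the required 50. This limits any claim about magnitude, but the plan itself expects groups to differ in size.

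Three stronger readings are tempting and not supported:
- A reader might infer that rare-device groups are over-filled with multi-device users. They are not: 71% expected against about 70% obtained. Random choice, at 55%, would represent those users less well.
- A reader might infer that the imbalance cannot be adjusted for. The article mentions recording the observed device but does not say that only this one is recorded. The full case report form is not shown, and the rule cannot be applied without establishing which types a person has.
- A reader might infer that the rarer-used device is always the one chosen. The criterion is the running recruitment count, so the choice can change during the study.

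Finally, nothing in the article says that multi-device users make more errors. If they do not, Check 3 shows no bias.

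**Conclusion.** The concern holds in a limited form. The statement that the rule spreads selection bias equally is wrong whenever recruitment is unequal: the rule balances counts and depletes the most commonly recruited groups of multi-device users, while rarer groups stay near their own users' share. In the scenarios run, the commonest group held anywhere from near 0% to about 70% multi-device users. The top of that range is the case with no gap to the other groups.

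Bias in the between-device comparison and in common-device prevalence is conditional. It needs unequal recruitment and a difference in errors between single-device and multi-device users. Under the assumptions used, half an extra error moved the false-positive rate little (7–10%), while one extra error raised it to about 26–27%. These are illustrations over assumed ranges, not estimates for this study. The point merits a change because the untrue claim bears on the primary comparison and the remedy is cheap.

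**What to change.** Keep the least-recruited rule, and justify it as a way to fill the quotas and remove discretionary choice. Withdraw the claim that it distributes selection bias equally. Then:

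1. Make sure all prescribed inhaler device types are recorded for each participant, with a look-up for those already enrolled, since recruitment has begun.
2. Report the share of multi-device users in each device group.
3. Supplement the one-way ANOVA or Kruskal–Wallis, neither of which takes this covariate as planned, with a sensitivity analysis of error counts adjusted for or stratified by one versus more than one device type. A count regression on device and multi-device use would serve. Include results in single-device users.

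The cost is one data item (if it is not already collected), the look-up and one additional model. Precision will be limited in the single-device subsets of the rarer groups: in the 60%-multi-device pattern, about 29% of 50, or roughly 15 people per group.

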### Recruitment

Participant recruitment into the study, undertaken by members of the research study team who are also part of the respiratory clinical care team at Queen Alexandra Hospital (Portsmouth Hospital University NHS Trust), will be via outpatient clinics, inpatient wards, research clinics in primary care, respiratory support groups, general practitioner (GP) practices as participant identification center ITE, social media feeds (Facebook and Twitter) of Portsmouth University Hospitals, staff and volunteers within the Trust, posters and flyers throughout the hospital, and the research database (in accordance with General Data Protection Regulation) compiled by the research department, which includes participants from previous research studies who have consented to be contacted for future studies.

Participants will be issued with a participant information sheet and will have adequate time to read this information before enrollment. Written consent will be obtained before undertaking any study-related activities.

Potential participants approached within clinical settings, who do not then consent to participate in the study, will be assured that nonparticipation will not affect their ongoing medical treatment, that their inhaler technique will be observed as per normal practice, and that they will be reeducated as necessary.

### Study Assessments

This section describes the information that will be recorded in the participant’s case report form (CRF), which will be anonymized using the participant’s unique study number.

#### Participant Clinical Characteristics

This includes patient demographics, such as age and gender, diagnosis requiring inhaler use, and comorbidities.

#### Disease Control Questionnaires

Disease control will be assessed using the ACQ for participants with asthma and the CAT for participants with COPD. For participants with a respiratory diagnosis other than asthma or COPD, this will be assessed by recording the number of exacerbations of their respiratory condition in the previous 12 months. An exacerbation is defined as an acute worsening of symptoms requiring treatment with antibiotics or oral corticosteroids. The ACQ [16] is a validated questionnaire for assessing the level of asthma control over the preceding 7 days. The ACQ-6 will be recorded if spirometry is not recorded for the purpose of the study, otherwise the ACQ-7 will be used. The COPD Assessment Test [17] is a validated, 8-item unidimensional measure of health status impairment in COPD. It assists patients and their physicians in quantifying the impact of COPD on the patient’s health. Responses are given on a 5-point scale, with a maximum total score of 40. The higher the score, the greater the impact COPD has on the patient’s health; scores of 0-9 are considered low impact; 10-20, medium; 21-30, high; and >30, very high.

